### 3.1 TRIAL OUTCOME MEASURES

Primary outcome measures will include diagnostic test characteristics (sensitivity, specificity, accuracy) for FDG-PET/CT and DCE-CT in relation to a subsequent clinical diagnosis of lung cancer. The outcome measures used in the economic model will include accuracy, estimated life expectancy, and quality adjusted life years (QALYs). Costs will be estimated from an NHS perspective. Incremental cost-effectiveness ratios will compare management strategies with DCE-CT to strategies without DCE-CT.

Secondary outcome measures will include diagnostic test characteristics for FDG-PET/CT with incorporation of CT appearances and combined DCE-CT/FDG-PET/CT. The incidence of incidental extra-thoracic findings on FDG-PET/CT, subsequent investigations and costs will also be determined.

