### 5.2 PATIENT MANAGEMENT FOLLOWING PET-CT AND DCE-CT

Following the PET-CT and DCE-CT investigations, management of the SPN should be directed by the local/specialist lung MDT.

In many cases nodule biopsy or excision biopsy may be undertaken. Those cases shown to be due to lung cancer (or other malignancy) will be managed according to local protocols. Follow up/outcome data will be collected by CRF.

In some cases it is recognised that nodule surveillance is appropriate (with or without prior biopsy). In these cases it is recommended that follow up is performed at

- 3 months
- 9 months
- 24 months

as per Fleischner Society Guidelines (Radiology 2005;237:395) for management of indeterminate nodules >8mm. (Deviation from these time points based on clinical need is at the discretion of the MDT)

At each visit the following should be performed:

- Chest CT (low dose, thin section, unenhanced) unless MDT feels it is inappropriate
- Recording of any biopsy samples taken

- Recording of health resource use information

At 2 years

- Health resource data will be collected from patient records
- The end of study CRF will be completed in the InForm Database
- The PI will sign off the patients electronic CRF record and the database will be locked for that patient

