## **7 DEFINITION OF END OF TRIAL**

This is a non-CTIMP study with all eligible patients recruited consecutively into the study and undergoing each study procedure. Recruitment will be terminated once 375 patients have been recruited and undergone a DCE-CT scan.

The study has two possible endpoints for each patient:

**Either** the diagnosis of lung cancer via biopsy **or** a diagnosis of benign or non- lung cancer via either biopsy (please note that in this case economic data collection will continue to be required for 2 years follow up)

**Or** failure of the imaged nodule to progress (increase in size) during the 2 year follow up period.

The end of the study will be reached when the last study patient reaches two years of follow up or withdraws full consent for continuing in the study.

**PLEASE NOTE:** *Health Resource Data will be collected for all patients over a 2 year period following the DCE-CT scan, therefore the end of study form will not be completed until this time unless patients have withdrawn full consent.*

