#### Quantitative analysis

Scans will be analysed and interpreted by PET-CT specialists at each centre.

Quantitative analysis of FDG-PET/CT data will consist of measurements of FDG uptake expressed as the maximum standardised uptake value (SUVmax).

The presence of incidental extra-thoracic findings on PET and maximal tumour diameter as measured by CT will be recorded.

The diagnostic performance of FDG-PET will be assessed with and without incorporation of the CT appearances using the guidelines in table 1 (secondary aim 1).

Based on previous studies [19, 20], the combined FDG-PET/CT assessment will be classified as positive for malignancy if one of the following criteria are met;

- grade 4 on FDG-PET,
- At least grade 3 on both modalities
- Grade 2 on PET and grade 3 or 4 on CT.

| Grade | Significance                 | FDG-PET                      | Attenuation Correction CT                                   |
|--------------|-------------------------------------|--------------------------------------------------|--------------------------------------------------------------------|
| 0            | No evidence of malignancy           | No visible uptake                                | Round, well defined lesion with laminated or popcorn calcification |
| 1            | Low probability of malignancy       | Uptake less than mediastinal blood pool          | Inflammatory features e.g. air bronchograms, enfolded lung         |
| 2            | Indeterminate                       | Uptake comparable to mediastinal blood pool      | Smooth well defined margins, uniform density                       |
| 3            | High probability of malignancy      | Uptake greater than mediastinal blood pool       | Lobulated, spiculated or irregular margins                         |
| 4            | Very high probability of malignancy | Evidence of distant metastases (i.e. M1 disease) | Evidence of distant metastases (i.e. M1 disease)                   |

Table 1: Guidelines for the interpretation of FDG-PET and Conventional CT

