## 8.7 ECONOMIC ANALYSIS

To evaluate the cost-effectiveness of the use of DCE-CT in the characterisation of SPNs, we will construct an economic model in accordance with current recommended best practice [23,26]. We propose a two stage format where a decision tree model will be developed to analyse the outcomes of diagnosis. The decision tree model will identify outcomes as: i) malignant SPN correctly diagnosed, ii) malignant SPN misdiagnosed as benign, iii) benign SPN correctly diagnosed, and iv) benign SPN misdiagnosed as malignant. The results of this will inform a Markov model to assess the longer term implications of diagnostic strategies. The Markov model will include health states for malignant disease at diagnosis (based on stage, i.e. local, regional or distant), recurrence (in patients treated with curative intent) and disease-free states (for patients with benign SPN and those with malignant disease who undergo successful surgery) as well as an absorbing “death” state. The perspective will be the NHS and Personal Social Services (PSS). In the long-term model costs and benefits will be discounted using standard rates (3.5%) [23].

Uncertainty relating to input parameters and assumptions will be explored using sensitivity analyses (deterministic, and where appropriate feasible probabilistic). The key variables to be explored will include: estimates of sensitivity and specificity of diagnostic strategies; prior probability (i.e. prevalence) of malignancy (including estimates for patients with SPN detected by CT screening as well as by clinical presentation), costs of diagnostic strategies, cost of curative treatment, probabilities of disease progression in patients with malignant disease and health related quality of life (associated with disease states and with curative treatment).

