#### Sample size consideration for each test separately

Published sensitivity for F-DG-PET for the characterisation of SPN vary between 77 and 96% (pooled weighted average: 92%) and specificity varies between 76 and 100% (pooled weighted average: 90%). Published sensitivity and specificity values for DCE-CT vary between 81 and 100% (pooled weighted average: 87%) and 29 and 100% (pooled weighted average: 83%) respectively. Based on two previous UK studies, the mean prevalence of malignancy in indeterminate SPN has been reported as 68.5% [18]. At this prevalence, a sample size of 375 will produce approximately 257 malignant and 118 benign SPNs. This will give confidence limits for sensitivity and specificity of DCE-CT of 87% +/- 4.1% and 83% +/- 6.8% respectively, with sensitivity and specificity values for F-DG-PET of 92% +/- 3.3% and 90% +/- 5.4% respectively. These estimates will provide sufficiently narrow confidence limits to allow precise economic modelling based on the results. For the purposes of economic analyses, we will also consider combining our data with the meta-analysis results from our systematic review (section 8.2), where previous studies we currently know about total 217 patients who had undergone both techniques [8-10]. Recruitment rates are anticipated to be high (70%) because DCE-CT will be additional rather than an alternative to normal care, and is readily incorporated into the existing PET-CT examination. We expect to recruit the required sample size (375) in 18 months. With a 70% recruitment percentage of all meeting the inclusion criteria, in order to recruit 375 patients we need to invite  $375/0.7 = 536$  patients.

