### Statistical analysis

#### (i) Diagnostic accuracy for 2 year follow-up

We will consider the diagnostic accuracy of positive FDG-PET and DCE-CT, both separately and in conjunction, in relation to a diagnosis of lung cancer by 2 years. In these analyses we will only be able to use those patients for whom the presence of lung cancer by 2 years is known; i.e. those without diagnosed lung cancer who drop-out before the end of 2 years will be excluded. This is likely to be small.

Initially, the separate diagnostic performance of FDG-PET/CT and DCE-CT will be examined using diagnostic criteria defined and over the full range of possible threshold values. At each threshold sensitivity and specificity will be estimated (with 95% confidence intervals), and the Receiver Operator Characteristic (ROC) curve will be calculated. The optimal cut-point from the range of values will be reported based on keeping the sensitivity above 90% and maximising specificity within this limitation. An alternative cut-point that provides the best trade off in sensitivity and specificity will also be reported. The sensitivity, specificity, positive predictive value (PPV) and negative predictive value (NPV) at these cut-points will then be presented with 95% confidence intervals. When translating sensitivity and specificity to PPV and NPV, we will need to assume a particular prevalence. This will be based on the prevalence in our study, and also we will report PPV and NPV for a range of other prevalence's reported in the literature (identified from our systematic review).

Secondly, the diagnostic performance of FDG-PET/CT and DCE-CT combined will also be examined using the same techniques as above; we will class patients as 'positive' if they have both FDG-PET and DCE-CT positive, and all others as 'negative'. Again, a range of different thresholds for both FDG and DCE will be considered.

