Thirdly, a logistic regression model will be considered including both PET and CT, on their original scale, as covariates. This may increase the power and diagnostic accuracy of identifying those who will subsequently be diagnosed with lung cancer. It will provide a risk score and predicted probability of lung cancer for each individual, based on their specific test values. We will then use a cut-off value to decide when a risk score is high (such that we predict an adverse outcome) and when it is low (such that we predict a good outcome). The calibration of the model will be assessed by grouping patients into deciles ordered by predicted risk and considering the agreement between the mean predicted risk and the observed number of true lung cancer cases in each decile (sometimes referred to as the expected versus observed statistic, E/O). The derived diagnostic rule will be cross validated by comparing the classification of each patient with their actual primary outcome of confirmed lung cancer, allowing an estimate of the sensitivity and specificity of the prediction model. Then, by varying the chosen cut-off level, we will produce a receiver operating characteristic (ROC) curve summarising the sensitivity and specificity of the predictive rule across the range of cut-offs. The overall discriminatory ability will be summarised as the Area Under ROC curve (AUC) with 95% confidence interval. The most suitable cut-off level can then also be detected. The internal validity of the final model will also be assessed by the bootstrap re-sampling technique to adjust for over-optimism in the estimation of model performance due to validation in the same dataset that was used to develop the model itself.

If the above methods all show poor accuracy performance (in terms of calibration and/or discrimination), then the logistic regression model will be extended to include additional patient-level covariates (such as time from FDG injection to PET-CT scan), in addition to test results. Demographic information will be considered here as well as clinical and imaging features considered indicative of a higher likelihood of SPN malignancy than unselected patients. The performance of the model will also be evaluated at the

practice-level where possible, to ascertain whether model performance is consistent in each practice or, if not, the variability in performance across practices, and whether it can be improved by tailoring the prevalence used in each practice.

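### Two target conditions for one 2×2 table: accuracy is scored against lung cancer, while test positivity, prevalence, precision and the economic model use malignant versus benign

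*Protocol*

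**What the plan says.** **Lung cancer as the target.** The primary outcome in section 3.1 (also in the synopsis and section 8.6) is test performance "in relation to a subsequent clinical diagnosis of lung cancer". The accuracy analysis in section 9.1 assesses the tests "in relation to a diagnosis of lung cancer by 2 years", and the prediction rule is checked against "their actual primary outcome of confirmed lung cancer". Section 7 names lung cancer on biopsy as one patient endpoint and sets against it "a diagnosis of benign or non- lung cancer via either biopsy".

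**Malignancy as the target.** Under section 8.1 the combined PET/CT reading "will be classified as positive for malignancy if one of the following criteria are met", and Table 1 grades probability of malignancy. Section 8.4 calls nodules with little growth benign. One branch of the section 8.7 decision tree is "malignant SPN misdiagnosed as benign". The sample size in section 9.1 starts from this: "the mean prevalence of malignancy in indeterminate SPN has been reported as 68.5"%. That gives 257 malignant and 118 benign nodules. The joint-test calculation also counts truly malignant tumours.

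**The two treated as one.** The sample size in Appendix 6 reuses 257 and 118 as lung cancers and non-malignant lesions. Appendix 5 poses its review question about malignancy but extracts 2×2 tables, and sets the accuracy outcome in its Table 3, on lung cancer.

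**Who can enrol.** Section 5.2 speaks of "Those cases shown to be due to lung cancer (or other malignancy". Section 4.3 excludes a history of malignancy only within the past 2 years. Section 4.2 also requires that there be no ancillary evidence strongly indicative of malignancy.

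**The concern.** Section 1.1 describes both tests as markers of malignancy (glucose metabolism for PET, neo-vascularisation for DCE-CT), not of lung origin. A solitary metastasis from an older or unrecognised primary, or another non-lung malignancy in the nodule, would therefore be expected to test positive. Scored against lung cancer it is a false positive. In the decision tree the same patient is a correctly diagnosed malignant nodule.

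The accuracy estimates feed that decision tree, so the input and the model would measure different things. The expected non-case group is small (118), so a few reclassified nodules move specificity noticeably. Left open, the choice of target could also be made after the results are known.

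**Working it through.** **Inputs, all from section 9.1 except the last.** N = 375 and prevalence of malignancy 0.685. PET sensitivity 0.92 and specificity 0.90. DCE-CT sensitivity 0.87 and specificity 0.83. Joint-test requirement 197 malignant, 288 in total. The share f of malignant nodules that are not lung cancer is not in the documents; 2%, 5% and 10% are assumed.

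**Step 1: reproduce the plan's figures.** 375 × 0.685 = 256.9, leaving 118.1, so 257 and 118. Half-width = 1.96 × √(p(1−p)/n), with n = 257 for sensitivity and n = 118 for specificity:
- DCE-CT: 4.11 and 6.78 points (stated 4.1 and 6.8)
- PET: 3.32 and 5.41 points (stated 3.3 and 5.4)

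The paired formula for a relative true-positive rate, two-sided 5% and 80% power, gives (2.80 / ln(0.88/0.92))² × (0.92 + 0.88 − 2 × 0.88)/(0.92 × 0.88) = 196.3, so 197; and 197/0.685 = 287.6, so 288. The arithmetic is sound, and all of it is on a malignant/benign basis.

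**Step 2: score against lung cancer as written.** Let k = f × 257, rounded, be the malignant nodules that move into the non-case group, testing positive at the stated sensitivity. Then

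apparent specificity = (118 × sp + k × (1 − se)) / (118 + k)

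| f | k | PET | shift | DCE-CT | shift |
|---|---|---|---|---|---|
| 0 | 0 | 90.0% | – | 83.0% | – |
| 2% | 5 | (106.2 + 0.40)/123 = 86.7% | 3.3 | (97.94 + 0.65)/123 = 80.2% | 2.8 |
| 5% | 13 | (106.2 + 1.04)/131 = 81.9% | 8.1 | (97.94 + 1.69)/131 = 76.1% | 6.9 |
| 10% | 26 | (106.2 + 2.08)/144 = 75.2% | 14.8 | (97.94 + 3.38)/144 = 70.4% | 12.6 |

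**Step 3: compare with the planned precision.** The shift equals k × (se + sp − 1)/(118 + k). It reaches the half-width h when k = 118h/(se + sp − 1 − h):
- PET: 118 × 0.054/(0.82 − 0.054) = 8.3 nodules, 3.2% of 257
- DCE-CT: 118 × 0.068/(0.70 − 0.068) = 12.7 nodules, 4.9% of 257

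At 2% both shifts are inside the half-widths. At 5% PET is clearly outside and DCE-CT only just.

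**Step 4: direction.** Specificity falls whenever non-lung malignancies test positive more often than benign nodules do, that is above 10% for PET and 17% for DCE-CT. The downward direction does not need the full stated sensitivities.

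**Step 5: what hardly changes.** With 244 lung cancers (5%) the sensitivity half-widths are 4.2 (DCE-CT) and 3.4 (PET); with 231 (10%) they are 4.3 and 3.5. Lung cancers fall below the 197 needed for the joint comparison only if more than 60 of the 257 (60/257 = 23%) are other malignancies. PET's specificity advantage over DCE-CT narrows from 7.0 points to 6.5, 5.8 and 4.8.

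**The case against.** The strongest reply is that the two terms are loose synonyms. Section 8.6 uses both in one paragraph, Appendix 6 treats them as the same, and section 8.4, which sets the reference standard, speaks of benign lesions and never puts a proven metastasis in the negative group. Section 7 is an end-of-trial rule with broken wording, not a coding rule for sensitivity and specificity. This stands to the extent that no section explicitly classifies a non-lung malignancy. A reader might infer that the plan deliberately codes metastases as negatives; the documents do not support that. But section 9.1 names lung cancer as the outcome, and an analyst who follows it reaches that coding.

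A second reply is that lung cancer is the stated indication. Against that target a PET-positive metastasis is a genuine false positive, so specificity is a different quantity and not a biased one. That is fair, and using lung cancer everywhere would also remove the contradiction. It would not match the positivity rule, the decision tree or the 68.5% prevalence as they stand.

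Third, the share is assumed, at 2% the shift is within the planned precision, and section 4.2 further limits such cases. All of this stands; section 4.2 reduces their number without removing them.

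Two further inferences go too far. One is that the systematic review works on malignant versus benign: its accuracy data are defined on lung cancer. The other is that a later cancer elsewhere in the lung would count as disease in a benign index nodule. Section 9.1 is worded by patient, but sections 7 and 8.4 follow the imaged nodule or lesion, so this is not established.

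**Conclusion.** The contradiction is real and lies in the protocol's own statement of its primary outcome, so it is not a detail that could be left to an analysis plan. Scored against lung cancer as written, specificity is lower than the malignant/benign specificity that the precision statement and the economic model assume. For a non-lung share of 2% to 10% the difference is about 3 to 15 points for PET and 3 to 13 points for DCE-CT. These sizes rest on two assumptions: the share, which the documents do not give, and positivity at the stated sensitivities.

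A reader might also infer that the sample size is wrong or the joint comparison underpowered. Neither follows: the stated figures reproduce, and sensitivity precision and joint-test power are little affected at these shares.

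**What to change.** Define the primary target condition as malignancy of the index nodule, whether primary lung cancer or another malignancy, and report lung cancer alone as a sensitivity analysis. Classify the final index-nodule diagnosis as lung cancer, other malignancy or benign. The CRF is not shown, so add this field only if it is not already captured.

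Use the same definition in the synopsis, sections 3.1, 7, 8.4, 8.6, 8.7 and 9.1, the 2×2 extraction and Table 3 in Appendix 5, and the 257/118 labels in Appendix 6. Appendix 5 has to move with the rest because section 9.1 considers combining the trial data with the review's meta-analysis for the economic work.

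The cost is minor rewording, one extra sensitivity analysis and possibly one CRF field. No extra patients or scans are needed. With malignancy as the single target, the stated 257/118 split and half-widths stand as they are.

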## 4. SELECTION AND ENROLMENT OF PATIENTS

### 4.1 SCREENING AND REGISTRATION

Patients will be identified either at local medical multi-disciplinary team (MDT) meetings or at the time of referral for investigation of SPN or at referral for FDG-PET/CT to the PET centres on the basis of having a single dominant pulmonary nodule on CT scan with uncertain aetiology, for which they will be referred for a FDG-PET/CT scan.

An ethically approved invitation letter may be sent to potential patients along with their FDG-PET/CT scan appointment letter inviting them to read the patient information sheet in advance of their appointment

and to contact the local research staff for further information and discussion about the trial should they wish to.

Local research and NHS staff will approach potential patients either in clinic or by phone to;

- Explain study and/or provide patient Information sheet
- Take age, sex and smoking history
- Confirm eligibility for study

Patients will be given an appointment for FDG-PET/CT scan and either booked for DCE-CT scan on the same day or within 14 days of the FDG-PET/CT scan appointment. (Note if there are scheduling issues scans may be up to a maximum of 21 days apart). Some sites may choose to make DCE appointment at FDG-PET/CT scan following consent if there are constraints on scanner time. In this case the DCE scan should still be scheduled within 14 days of the FDG-PET/CT scan.

SPUtNIK Patient information sheets and IPCARD-SPN questionnaire will be given to patients either in clinic or by post.

## **4.2 INCLUSION CRITERIA**

- A soft tissue solitary dominant pulmonary nodule of  $\geq 8\text{mm}$  and  $\leq 30\text{mm}$  on axial plane
  - Measured on lung window using conventional CT scan
  - No other ancillary evidence strongly indicative of malignancy (e.g. distant metastases or unequivocal local invasion)
- If clinicians and reporting radiologists believe the patient is being treated as having a single pulmonary nodule and there are other small lesions  $<4\text{mm}$  that would normally be disregarded, the patient should be included in the trial.
- Nodules already under surveillance can be included provided they have a recent or scheduled FDG-PET/CT
- 18 years of age or over at time of providing consent
- Able and willing to consent to the study.

